### 4.2. Exercise-Induced Glycogen Depletion (80–90 Min)

The exercise protocol, adapted from seminal glycogen depletion studies [27,28], will take place after participants arrive for the start of the fasting visit following an overnight fast and after all initial assessments are complete. Power outputs for the cycle ergometer will be determined based on the incremental VO_2_peak test performed during the screening visit. Participants will engage in 60 min of cycling at a constant power output corresponding to 60–70% of their peak VO_2_, maintaining a cadence of 60–70 rpm, which is classified as moderate-intensity physical activity. After a 5 min rest, the participants will perform repeated 1 min sprints at 90 rpm and 90–100% of their VO_2_peak equivalent power output, with 1 min rest intervals between sprints. The exercise session will conclude after ten sprints or if participants cannot maintain a pedalling rate of ≥80–90 rpm for 1 min. Verbal encouragement will be provided throughout the session, during which heart rates will be recorded using Polar H10 chest strap heart rate monitors. Throughout the exercise session, participants’ fatigue levels will be monitored using the Rating of Perceived Exertion (6–20 RPE) scale, with heart rate and RPE recorded every 10 min during steady-state cycling and after each sprint. The exercise will be terminated if participants report severe fatigue (RPE ≥ 19), experience any adverse symptoms (dizziness, nausea, unusual shortness of breath), or if heart rate exceeds 95% of age-predicted maximum for more than 3 min. If a participant cannot complete the full protocol, a minimum of 60 min of steady-state cycling plus three sprints will be considered sufficient for partial glycogen depletion, allowing continued participation in the study. Those unable to meet these minimum requirements will be withdrawn from this arm of the trial.

## 5. Outcomes

### 5.1. Primary Outcome

The primary outcome will be the measurement of autophagy activation in isolated PBMCs from healthy individuals who have undergone a three-day water-only fast, with or without a single session of glycogen-depleting exercise using the methodology described previously [29].

### 5.2. Secondary Outcomes

Secondary outcomes to be assessed include:Body weight, waist circumference, and body composition measured by DXA and Bod Pod;Autonomic function, including heart age and heart rate variability, assessed through resting electrocardiography;Blood pressure;Endothelial function evaluated by flow-mediated vasodilation;Continuous monitoring of blood glucose kinetics;Capillary ketones and glucose levels using a portable test strip-based meter;Oral glucose tolerance test to assess glucose tolerance and insulin action;Serum fasting free fatty acids, BHB, acetoacetate, BHB-to-acetoacetate ratio, and lipid profile;Serum concentration of insulin, IGF-1, IGFBP-1, IGFBP-2, IGFBP-3, FGF21, cortisol, testosterone, estradiol, sex hormone-binding globulin (SHGB), T3, Klotho, BDNF, and Beta-Amyloids (Aβ40 and Aβ42);Markers of inflammation, including high-sensitivity C-reactive protein, cytokines (IL-6, TNF-alpha), and chemokines (MCP1);Markers of oxidative stress, including urinary F-2 isoprostanes and 8-hydroxy-2′-deoxy Guanosine.

### 5.3. Exploratory Outcomes

Several exploratory outcomes will also be examined:Levels of autophagy cargo receptor proteins in PBMCs such as p62/SQSTM1, NBR1, and OPTN;Calculated adjusted autophagy score based on (a) the primary outcome, (b) changes in PBMC pool make up, and (c) pre-existing data from cell type-specific autophagy calculated using flow cytometry;Plasma proteomics using Olink’s Proximity Extension Assay (PEA) technology to detect over 5400 proteins;Mass spectrometry-based proteomics and metabolomics of PBMCs;Plasma lipidomics and metabolomics;Detailed profiling of circulating immune cell populations and their functional states, along with molecular markers assessed via flow cytometry, including the lymphoid/myeloid ratio and a marker of protein acetylation in B cells;DNA methylation and genomic analysis in isolated PBMCs and buccal mucosa cells, including methylation-based ageing biomarkers such as DunedinPACE and GrimAge;Platelet characterisation involving proteomic analysis, flow cytometry, and activation assays to elucidate biochemical composition, surface marker expression, and functional responsiveness;Characterisation of plasma extracellular vesicles (EVs) using nanoparticle tracking analysis, transmission electron microscopy, and the proteomics of isolated EVs to determine size distribution, morphology, and cargo composition;Analysis of the gut microbiome through 16S ribosomal RNA (rRNA) gene amplicons and shotgun metagenomics.

### 5.4. Safety Monotoring and Reporting

Participant safety is prioritised through comprehensive screening, monitoring, and risk mitigation strategies. Screening excludes individuals with conditions that could increase risk, including a history of hypoglycemic episodes, cardiovascular problems, or eating disorders. During the fasting period, participants are monitored via continuous glucose monitoring, additional twice-daily glucose and ketone measurements, and regular check-ins with study staff. Medical supervision is provided during exercise sessions, with clear stopping criteria based on heart rate, blood pressure, and symptoms. Emergency protocols include immediate exercise termination criteria and breaking-fast procedures if participants experience severe adverse effects. Adverse events (AE) and serious adverse events (SAE) will be systematically documented and reported throughout the study to prioritise participant safety. Each event will include details such as a description, onset date, end date, severity, assessment of relatedness to the trial intervention or device, and any actions taken in response. Research investigators will use their clinical expertise to determine whether an AE necessitates the participant’s removal from the study. SAEs will be reported to the primary investigator within 24 h of the study team’s awareness. The complete course of the SAE, including any administered therapy, will be communicated to the study sponsor. Additionally, any significant safety concerns will be reported to the local Human Research Ethics Committee and Research Governance Officers.

### 5.5. Sample Size Calculation

A total of 25 volunteers will be recruited for the study. Given the crossover design, each participant will undergo both interventions, effectively creating two groups of 25. To estimate the required sample size, the change in LC3B-II to beta-actin ratio was considered. LC3B-II, the lipidated form of microtubule associated protein 1 light chain 3 beta that accumulates on autophagosomes when lysosomal degradation is blocked, is the gold standard marker for measuring autophagic flux in human samples [30]. Utilising ANOVA with a repeated measures design, assuming a standard deviation of 95.4, and aiming for 80% power at a significance level of 0.05, a difference of 30% (a change of 134.7 from a mean of 299.3 ng/mg protein/hour in the control group at baseline) could be detected with a sample size of 20 per group. Accounting for an estimated dropout rate of 20%, the initial recruitment target is set at 25 participants, based on the study by Bensalem et al. [29]. Sample size versus power plot is shown in Supplementary Figure S1. Additionally, sensitivity analyses, examining sample size requirements for detecting 20% and 40% changes, are shown. The exploratory outcomes will not be separately powered but will provide valuable hypothesis-generating data for future targeted studies.

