## 2. Aims of Profasta Trial

The primary aim of the PROFASTA trial is to evaluate the impact of a three-day water-only fast, with and without a single session of glycogen-depleting exercise, on autophagic flux in isolated peripheral blood mononuclear cells (PBMCs) where flux is measured by the introduction of a lysosomal inhibitor into whole blood. The primary hypothesis is that glycogen depletion through exercise prior to fasting will significantly enhance autophagic activation in PBMCs. Secondary objectives include assessing changes in body composition, heart rate variability, endothelial function (measured via flow-mediated vasodilation), as well as plasma metabolomic and proteomic shifts, and microbiome metagenomic adaptations in stool samples.

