## 3. Methods

### 3.1. Study Design

The PROFASTA trial is a randomised, single-centre, two-period, two-sequence crossover study, involving a total sample of 25 participants. Participants will be randomly assigned into two groups, with each group undergoing two different interventions in separate phases (Figure 1). By the study’s end, all participants will have completed both Intervention A and Intervention B, ensuring robust within-subject comparisons to strengthen the validity of the findings. Intervention A consists of a three-day water-only fast, while Intervention B includes a three-day water-only fast that is preceded by a single session of glycogen-depleting endurance exercise conducted on the first day of the fasting period, following an overnight fast. Detailed clinical visits and procedures are outlined in Table 1 and Table 2. This study has been approved by the Sydney Local Health District Ethics Committee (2022/ETH00617), and all study visits will take place at the Charles Perkins Centre-Royal Prince Alfred Hospital (CPC-RPA) clinic. The protocol has been prepared using the SPIRIT reporting guidelines [26].

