Fasting for several days can be extremely challenging, so any intervention that could accelerate or potentiate this process would be beneficial. Ketosis typically begins when glycogen stores become depleted and cannot provide sufficient glucose for the brain, which cannot utilise lipids or proteins for energy [3]. Intense exercise can rapidly deplete glycogen stores, particularly in muscle tissue, as glycogen is the primary fuel source during prolonged or high-intensity physical activity [33,34,35]. During high-intensity, intermittent endurance exercise (above 75% VO_2_peak), marked reductions in glycogen stores occur within 30–60 min [36,37]. This is because such intense activity places a high energy demand, causing muscles to rely heavily on glycogen as a primary fuel source. This depletion forces the body to shift towards alternative energy sources, such as fatty acids and ketone bodies, which can accelerate metabolic adaptations like ketosis. Our primary hypothesis is that glycogen depletion through exercise prior to fasting will significantly amplify autophagy activation and other molecular pathways that slow ageing processes, compared to fasting alone.

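### Section 5.5 does not establish 80% power for the primary within-participant contrast, fast plus exercise minus fast alone

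*Protocol article*

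**What the plan says.** Section 3.1 describes a "randomised, single-centre, two-period, two-sequence crossover study, involving a total sample of 25 participants". Section 2 sets the primary hypothesis that "glycogen depletion through exercise prior to fasting will significantly enhance autophagic activation in PBMCs", and the Discussion names the comparator: "compared to fasting alone". The primary test is therefore Intervention B minus Intervention A within participant.

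Section 5.5 justifies the sample size as follows.

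- The crossover is counted as one where "each participant will undergo both interventions, effectively creating two groups of 25", and the required size is given as 20 per group.
- The measure is introduced with "the change in LC3B-II to beta-actin ratio was considered", but the mean of 299.3 is in ng/mg protein/hour.
- The calculation is described as "Utilising ANOVA with a repeated measures design", "assuming a standard deviation of 95.4, and aiming for 80% power at a significance level of 0.05".
- The effect is a 30% difference, glossed in the same sentence as a change of 134.7 from the control group's baseline mean of 299.3.
- A 20% dropout allowance takes 20 to 25.

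**The concern.** The power of a paired contrast depends on two quantities: the expected B-minus-A difference and the SD of that difference within a participant. Section 5.5 states neither in recognisable form. The value 95.4 could be a between-person SD, a within-person SD or the SD of a difference, and the text gives no within-participant correlation. The effect is expressed relative to a baseline mean, and nothing says that it is what exercise adds to the fast. The text also leaves open whether end-of-fast values or changes from each period's baseline are meant. The two printed effect sizes disagree with each other.

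This is the only justification for the number of participants on the primary outcome. If B and A turn out similar, a reader cannot tell from section 5.5 what added effect of exercise the trial was able to detect.

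**Working it through.** **Inputs from section 5.5:** SD 95.4; baseline mean 299.3; effect 30% or 134.7; 80% power; alpha 0.05; n = 20; dropout 20%. **Assumed:** two-sided test; 95.4 is the SD at a single visit; one common correlation rho between any two visits of the same person, taken as 0, 0.3, 0.5 and 0.7 because the article gives none.

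**Step 1, the effect.** 0.30 × 299.3 = 89.8. But 134.7 / 299.3 = 0.450. The two printed figures are 30% and 45%.

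**Step 2, reproducing the plan's 20.**

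- Independent two-sample t test, 89.8: 19 per group reach 80%; power at 20 per group is 83%.
- Paired crossover with 95.4 as the within-person SD (the same as rho = 0): SD of the difference = 95.4 × √2 = 134.9; non-centrality = 89.8 / (134.9 / √20) = 2.98; 18 df; critical t = 2.10; power 80.4%. With 19 participants it is 78.1%, so 20 is the smallest sufficient number.
- Changes from period baseline with rho = 0.5: SD = 2 × 95.4 × √0.5 = 134.9, hence again 80.4% at 20.
- With 134.7 in place of 89.8: 9 per group (independent), 11 participants (paired, rho = 0) or 18 participants (changes, rho = 0), and fewer at higher rho in the paired cases. None of these gives 20.
- Dropout: 20 / 0.80 = 25, as printed.

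So 20 is reached from 89.8, by more than one route, and not from 134.7 by any of these routes.

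**Step 3, power for B minus A with 20 completers.** Non-central t with n − 2 = 18 df.

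- End-of-fast values: SD of difference = 95.4 × √(2(1 − rho)).
- Changes from period baseline: SD of difference = 95.4 × √(4(1 − rho)).

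| rho | SD, end-of-fast | Power, 89.8 | n for 80% | SD, changes | Power, 89.8 | n for 80% |
|---|---|---|---|---|---|---|
| 0 | 134.9 | 80% | 20 | 190.8 | 51% | 38 |
| 0.3 | 112.9 | 92% | 15 | 159.6 | 66% | 27 |
| 0.5 | 95.4 | 98% | 12 | 134.9 | 80% | 20 |
| 0.7 | 73.9 | 99.9% | 8 | 104.5 | 95% | 13 |

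With 134.7 the lowest power in each column, at rho = 0, is 98.8% for end-of-fast values and 84.7% for changes.

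If 95.4 is instead already the SD of the paired difference, 12 participants suffice for 89.8 and power at 20 is 98%.

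**Step 4, what 20 completers can detect at 80% power.** End-of-fast values: 89, 75, 63 and 49 ng/mg protein/hour for rho 0, 0.3, 0.5 and 0.7 (30%, 25%, 21% and 16% of 299.3). Changes: 126, 106, 89 and 69 (42%, 35%, 30% and 23%).

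**The case against.** The strongest reply is that the calculation may well have been a proper crossover calculation. Section 5.5 names a repeated-measures design, recruits 25 people and not 50, and applies dropout to people. If 95.4 is the within-person SD, the paired test with a difference of 89.8 needs exactly 20, which fits the printed number slightly better than the independent test's 19. On that view the two-group phrase is loose wording with no numerical effect. The article is also a condensation: Supplementary Figure S1 and the sensitivity analyses for 20% and 40% are not shown and may state the correlation or the type of SD. Nor does the text say that the 30% is the response to fasting; it may be meant as the B-minus-A difference, with the baseline mean used only to form the percentage.

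Most of this stands, and it rules out two stronger readings that a reader might draw. One is that the stated 80% is simply not the power of the primary test, or that 20 comes only from a two-group calculation. The paired routes in the working show otherwise. The other is that the trial is underpowered. For end-of-fast values and 89.8, any positive correlation lifts power above 80%, and with 134.7 power exceeds 80% throughout the range examined. For 89.8, power falls short only if changes are compared and the correlation is below about 0.5; otherwise the true difference between the fasts would have to be below about 90.

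The reply does not repair the paragraph. The routes that give 80% at 20 need 89.8 and not the printed 134.7, and each needs an assumption that the text does not state. Nothing in a supplementary plot would make 134.7 equal to 30% of 299.3, or make a beta-actin ratio and ng/mg protein/hour the same scale.

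**Conclusion.** The point holds in a limited form. As printed, the inputs of section 5.5 do not establish 80% power for the primary contrast. Across the undefined choices, the number needed to detect 89.8 runs from 8 to 38 and the power of 20 completers from 51% to 99.9%. These ranges rest on a per-visit SD of 95.4, equal correlation between visits, rho from 0 to 0.7 and a two-sided 5% test. The disagreement between 30% and 134.7 and the mixed units need no assumption.

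Severity is moderate: the justification needs correcting, but nothing here shows that 25 is too few.

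**What to change.** Rewrite the calculation in section 5.5 and keep the recruitment target.

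- State the target as the B-minus-A difference within participant, and say whether the primary analysis compares end-of-fast values or changes from period baseline.
- Give the SD of that within-participant difference, or the per-visit SD with a range of correlations, and say which SD 95.4 is.
- Reconcile 30% with 134.7.
- Give the endpoint, its mean and its SD in one unit.
- Remove the statement about two groups of 25 and the per-group wording.
- If Supplementary Figure S1 already states a correlation, quote it in the text.

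Possible wording, if 95.4 is the per-visit SD: *With 20 completers, the paired comparison of end-of-fast values has 80% power for a difference between the two fasts of 75, 63 or 49 ng/mg protein/hour at within-participant correlations of 0.3, 0.5 or 0.7.* If changes from period baseline are analysed, the corresponding figures are 106, 89 and 69.

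The cost is one paragraph and a short recalculation, with no change to recruitment or conduct.

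### The detectable effect is given as 30% and as 134.7, but 134.7 is 45% of the stated mean of 299.3, and 20 per group at 80% power matches 89.8, not 134.7

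*Protocol article*

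**What the plan says.** The only power statement is in section 5.5 (Sample Size Calculation) of the protocol article. It gives:

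- the method: "Utilising ANOVA with a repeated measures design";
- the variability: "assuming a standard deviation of 95.4";
- the error rates: "aiming for 80% power at a significance level of 0.05";
- the effect: "a difference of 30% (a change of 134.7 from a mean of 299.3 ng/mg protein/hour in the control group at baseline");
- the result: this "could be detected with a sample size of 20 per group";
- the allowance for losses: "Accounting for an estimated dropout rate of 20%, the initial recruitment target is set at 25 participants".

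The section also says that sensitivity cases for 20% and 40% changes accompany a power plot in a supplement, which is not shown. It does not say whether 95.4 is a between-subject SD, a within-subject SD or the SD of paired differences, nor whether the test is one- or two-sided.

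**The concern.** The sentence presents a relative and an absolute effect as the same quantity, measured from the same mean. They are not the same: one is half as large again as the other. The stated sample size can follow from at most one of them.

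Section 5.6 relies on this calculation when it describes the sample size as powered for the primary outcome, so the error affects how the trial will be read. The primary hypothesis is that exercise before the fast adds to the autophagic response. If no such difference is found, readers will ask how large a difference the trial could have detected. The sentence offers 89.8 (through the percentage) and 134.7 (in absolute units). If 134.7 was the real input, the stated number and power do not follow from it. If 30% was the input, the absolute effect is overstated by 50%.

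**Working it through.** **Inputs** (all from section 5.5): control mean 299.3; relative effect 30%; absolute effect 134.7; SD 95.4; alpha 0.05; power 0.80; 20 per group; dropout 20%. I assume a two-sided test unless stated otherwise.

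**1. Percentage against absolute change**

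- 0.30 × 299.3 = 89.8
- 134.7 / 299.3 = 0.450
- 0.45 × 299.3 = 134.685, which rounds to 134.7, so the printed change is 45% of the printed mean to the last digit.
- For 134.7 to be 30%, the mean would have to be 134.7 / 0.30 = 449.0, which is 1.5 × 299.3. The article gives no such mean.
- Taking the post-change value as denominator does not help: 134.7 / (299.3 + 134.7) = 134.7 / 434.0 = 31.0%.
- Ratio of the two effects: 134.7 / 89.8 = 1.50.

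**2. Reproducing the stated 20 per group**

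Normal approximation for two means: n per group = 2 × (1.960 + 0.842)² × (SD/Δ)² = 15.70 × (95.4/Δ)².

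- Δ = 89.8: 15.70 × (1.062)² = 17.7, so 18
- Δ = 134.7: 15.70 × (0.708)² = 7.9, so 8

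Exact versions use the noncentral t distribution. For the crossover, with 95.4 as the within-subject SD, the SD of a paired difference is √2 × 95.4 = 134.9.

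| Reading of the calculation | n for 89.8 | Power at 20 | n for 134.7 | Power at 20 |
|---|---|---|---|---|
| Two samples, normal approximation | 18 | 0.845 | 8 | 0.994 |
| Two samples, t | 19 | 0.826 | 9 | 0.992 |
| Crossover, 95.4 within-subject, t | **20** | 0.806 | 10 | 0.988 |

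The stated 20 is recovered exactly with 89.8 in the crossover reading and to within one or two in the others. With 134.7 the requirement is about half of 20. One-sided tests lower every figure: 15 (two-sample t) and 16 (crossover) for 89.8, and 7 and 8 for 134.7.

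**3. The same check in reverse**

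- Difference detectable with 20 at 80% power: 84.5 (normal), 86.7 (two-sample t) and 89.1 (crossover), which is 28% to 30% of 299.3.
- For 134.7 to need 20, the SD would have to be about 148 (two samples), or the SD of paired differences about 204. The stated SD is 95.4.

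**4. Less usual readings of 95.4**

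- As the SD of paired differences: n = 11 for 89.8 and 7 for 134.7. Neither gives 20.
- As the SD of a single measurement, with the contrast a within-person difference of two changes from baseline and no correlation between measurements: SD = 2 × 95.4 = 190.8, so n = 18 for 134.7 (power 0.849 at 20) and n = 38 for 89.8 (power 0.515 at 20). With a correlation of 0.5 this becomes n = 10 for 134.7 and n = 20 for 89.8. To push 134.7 up to 20, the correlation would have to be negative (−0.2 gives 21).

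**5. Dropout**

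20 / (1 − 0.20) = 25. This step is correct whichever effect was meant.

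**The case against.** The strongest reply is that the design itself is unharmed. Taking 30%, SD 95.4, 80% power and alpha 0.05, the calculation gives 19 or 20, and 25 follows after dropout. The fault then lies in one absolute figure in a parenthesis, and no design decision depends on it. The 20% and 40% sensitivity cases support this, because they bracket 30% and would leave a 45% base case outside their range. Nothing in the article sets a success or futility rule using 134.7.

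Most of that stands as a reading of what was probably meant. It does not make the sentence correct. The printed absolute change still contradicts the printed percentage, and nothing elsewhere in the article settles which is right.

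A second reply is that the type of SD is not stated, so the claim that 20 fits only 89.8 is conditional. That is fair. If 95.4 is the SD of paired differences, neither effect gives 20. The section speaks of a change in the marker ratio, so a change-score calculation cannot be ruled out, although none is described. With uncorrelated measurements it would bring 134.7 to 18, close to 20, and leave 89.8 with power of only about 0.52. This possibility is a reason to trace the original inputs before simply replacing 134.7 with 89.8. It does not remove the conflict between 30% and 45%.

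Finally, the supplement is not shown, so nothing establishes that its plot or sensitivity cases carry the same error. They need checking on that account.

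**Conclusion.** The concern holds. Section 5.5 equates a 30% difference with a change that is 45.0% of its own stated mean. With a two-sided 5% test and 95.4 as a between- or within-subject SD, 20 per group at 80% power corresponds to 89.8 (19 or 20 needed by the t calculations). A change of 134.7 would need 9 or 10 and would have power of about 0.99 at 20.

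The arithmetic of 30% against 45% rests on no assumption. The match between 20 and 89.8 depends on the type of SD, which the article does not state. The best-supported explanation is that 30% was the input and 134.7 is the wrong figure. In that case the statement is wrong as printed, but the target of 25 is sound.

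**What to change.** Retrieve the original calculation and restate section 5.5 with one consistent set of inputs:

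- If 30% was the input, give the change as 89.8 from 299.3. This supports 20 per group and 25 recruited.
- If 134.7 was the input, call it a 45% difference and restate the power at 20 (about 0.99 under the two-sample and crossover readings above), or give the contrast and SD that actually produced 20.
- If the mean is the wrong figure, correct it from the source data and recompute.

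In the same sentence, say what kind of SD 95.4 is and whether the test is two-sided.

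Check Supplementary Figure S1 and the 20% and 40% cases against the corrected inputs, and rerun them. From a mean of 299.3 these are changes of 59.9 and 119.7, which need 42 and 13 participants in the crossover reading, or 41 and 12 per group as two samples.

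The cost is one corrected sentence and one rerun of the supplementary plot. Recruitment does not change.
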